### Functional analysis

3.4

Beyond univariate analyses, we will characterize the large-scale neural dynamics underlying depth of anesthesia by constructing functional connectivity networks for each stimulation block. Connectivity will be computed using weighted phase lag index (wPLI) (Vinck et al., 2011), where EEG data will first be filtered into canonical frequency bands (delta 1–4 Hz, theta 4–8 Hz, alpha 8–14 Hz, beta 14–30 Hz).

The wPLI isdefined as: 
$\mathrm{wPL}I_{\mathrm{ij}}=\frac{E\{ℑ(C_{\mathrm{ij}})\}}{E\{|ℑ(C_{\mathrm{ij}})|\}}=\frac{E\{|ℑ(C_{\mathrm{ij}})|\mathrm{sgn}(ℑ(C_{\mathrm{ij}}))\}}{E\{|ℑ(C_{\mathrm{ij}})|\}}$
,

where 
$ℑ(C_{\mathrm{ij}})$
 is the imaginary part of cross-spectrum the imaginary component of the cross-spectrum between signals *i* and *j*. The cross-spectrum is defined as C_ij_ = Z_i_Z_j_, with Z_i_ and Z_j_ denoting the Fourier spectrum of channel *i* and the conjugate spectrum of channel *j*. The wPLI values range from 0 (no consistent lag/lead relationship) to 1 (perfect non-zero phase locking) (Vinck et al., 2011).

To assess the directionality of functional connectivity, we will compute the directed phase lag index (dPLI) (Stam and Van Straaten, 2012). The instantaneous phase of each EEG channel will be extracted using a Hilbert transform. For each time point *t*, the phase difference between channels *i* and *j* will be computed as 
$\Delta \phi_{t}=\phi_{i,t}-\phi_{j,t}$
.

The dPLI is then given by: 
$\mathrm{dPL}I_{\mathrm{ij}}=\langle H(\Delta_{\mathrm{\varphi t}})\rangle$
,

where *H(x)* is the Heavyside step function: 
H(x)=1ifx>0,H(x)=0.5ifx=0,andH(x)=0
 otherwise. dPLI values >0.5 indicate that channel *i* consistently leads channels *j*, whereas values <0.5 indicates the opposite.

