### Graph theoretical properties

3.5

For each frequency band, wPLI matrices will be thresholded into adjacency matrices, and graph-theoretical analyses will be performed. Core measures will include global efficiency (Latora and Marchiori, 2001), clustering coefficient (Watts and Strogatz, 1998), modularity (Newman, 2006), and small-worldness (Humphries and Gurney, 2008). Network hubs will be identified using node degree and betweenness centrality, reflecting the integration role of highly connected nodes (Van Den Heuvel and Sporns, 2013). Particular focus will be given to frontoparietal connectivity, which is strongly implicated in anesthetic-induced unconsciousness (Lee et al., 2013).

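### The printed wPLI formula is signed and runs from -1 to +1, which contradicts the 0-to-1 range stated beside it

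*Protocol article*

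**What the plan says.** Section 3.4 of the protocol article gives wPLI in two forms. In the notation used here, with C for the cross-spectrum of channels i and j, they are E{Im C} / E{|Im C|} and E{|Im C| sgn(Im C)} / E{|Im C|}. Neither numerator is enclosed in an absolute value.

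The cross-spectrum is a product, "with Z_i_ and Z_j_ denoting the Fourier spectrum of channel *i* and the conjugate spectrum of channel *j".

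The scale is then stated: "The wPLI values range from 0 (no consistent lag/lead relationship) to 1 (perfect non-zero phase locking".

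Section 3.5 (Graph theoretical properties) says what is done with the result: "wPLI matrices will be thresholded into adjacency matrices, and graph-theoretical analyses will be performed". Global efficiency, clustering, modularity, small-worldness and hub measures follow from those matrices.

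Direction is handled by a separate index, dPLI. On the phases, section 3.4 says: "The instantaneous phase of each EEG channel will be extracted using a Hilbert transform". A plain difference of the two phases goes into a Heaviside step, and the reading is: "dPLI values >0.5 indicate that channel *i* consistently leads channels *j*, whereas values <0.5 indicates the opposite".

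**The concern.** A ratio of the mean of a signed quantity to the mean of its absolute value can be negative. An index described as going from no consistent lag to perfect locking on a 0-to-1 scale cannot. Formula and scale stand in the same section and disagree.

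This matters because the matrix is thresholded. A cut-off applied to an unsigned index selects pairs by strength of coupling. The same positive cut-off applied to a signed index keeps a pair in one channel order and drops it in the other, according to which channel leads. The network hypotheses under Specific Aim 2 (section 1.8) and the predictions in section 4.4 (frontoparietal connectivity, global efficiency, modular segregation, small-worldness) would then rest on edges partly decided by how the channels happen to be numbered. The abstract lists these as secondary outcomes.

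**Working it through.** **Inputs from the document.** The two forms of wPLI, the cross-spectrum with the conjugate on channel j, the 0-to-1 range (all section 3.4), and the thresholding step (section 3.5).

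**Inputs assumed.** Lags, phase-noise levels, 64 channels and a cut-off of 0.3. The article gives none of these for the index (its EEG net has 128 channels), so the simulated counts are illustrative.

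**Step 1: the two printed forms are the same quantity.** For any real Y, |Y| sgn(Y) = Y. With Y = Im C, the second numerator equals the first. The forms agree with each other and conflict only with the stated range.

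**Step 2: range.** Since |E{Y}| ≤ E{|Y|}, the ratio E{Y} / E{|Y|} lies between -1 and +1. It reaches +1 when Y is always positive and -1 when Y is always negative.

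**Step 3: channel order.** Write X for the Fourier spectrum of a channel and * for the conjugate. Then C_ij = X_i X_j* and C_ji = X_j X_i* = (C_ij)*. Hence Im C_ji = -Im C_ij. The numerator changes sign, the denominator does not, and wPLI_ji = -wPLI_ij.

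**Step 4: numerical check of the printed formula.**

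| Simulated pair | wPLI (i,j) | wPLI (j,i) | Stated scale |
|---|---|---|---|
| Constant lag, no noise | +1.000 | -1.000 | 1 in both orders |
| Lag π/4, phase noise SD 1.0 rad | +0.674 | -0.674 | same value between 0 and 1 in both orders |

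The stated range is therefore not reproduced by the printed formula.

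**Step 5: thresholding.** In a simulated 64-channel matrix (lags uniform between -π/2 and π/2, phase noise SD 0.8 rad), the printed formula gave values from -0.83 to +0.83. The matrix was antisymmetric to rounding error, with an off-diagonal mean of 0 and a mean absolute value of 0.52.

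- Pairs with |wPLI| > 0.3: 1,576.
- Upper-triangle entries with signed wPLI > 0.3: 774, which is 774 / 1,576 = 49%.
- The other 1,576 - 774 = 802 pairs lie below -0.3 in that triangle and pass only in the opposite channel order.

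The thresholded matrix is not symmetric. Software that reads one triangle would lose about half of the edges here. Software that reads the whole matrix would see a directed graph.

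**Step 6: with the absolute value restored.** |E{Im C}| / E{|Im C|} lies between 0 and 1, is the same in both channel orders, and keeps all 1,576 pairs.

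**Step 7: dPLI.** Suppose phases are taken as principal values and their difference is not re-wrapped. For a constant lead θ the index is then 1 - θ/(2π): 0.984 at 0.1 rad, 0.875 at π/4, 0.750 at π/2 and 0.625 at 3π/4. A re-wrapped difference gives 1.000 throughout. For every lead below 180° the first version stays above 0.5, so the only reading the article gives, the direction about 0.5, is kept. Continuously unwrapped phases behave differently. In 180 s of simulated 1–4 Hz noise at 500 Hz they gave values from 0.0 to 0.965, often on the wrong side of 0.5, because of arbitrary 2π offsets. The article does not say which convention is used.

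**The case against.** The best defence is that section 3.4 settles the intent itself. It states an unsigned 0-to-1 scale and then brings in a separate index for direction, so wPLI is plainly meant to be non-directional. The missing bars are then a slip of notation, and nothing shows that the custom scripts repeat it. The type of threshold is not given either, so the loss of edges is conditional. All of this stands, and it is why the point is rated low.

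It does not remove the point. The formula is what the article gives an analyst to implement, and it is wrong as printed. Loss of symbols in reading the PDF is an unlikely explanation: the inner bars and the denominator bars survive, and the outer bars are absent from both forms.

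A reader might infer more than the article supports:

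- **That a stated dPLI scale is contradicted too.** The article gives dPLI no magnitude scale, only a direction about 0.5. How the phase difference is wrapped is a detail that an article may leave to the full plan or the code.
- **That the graph measures depend on dPLI.** Section 3.5 builds them from wPLI alone.
- **That in-phase stimulation is expected to reverse lag direction and so create or delete edges.** Sections 1.8 and 4.1 expect posterior spread and anterior-to-posterior waves with in-phase stimulation. Section 1.8 assigns disrupted propagation to anti-phase. No in-phase reversal is predicted.
- **That averages over frontoparietal pairs must cancel to zero.** Cancellation is guaranteed only when both channel orders are averaged. With a fixed frontal-to-parietal order and a consistent lag, the signs agree.

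**Conclusion.** The wPLI definition and its stated range are inconsistent. This follows from algebra on the article's own formula and needs no assumption beyond reading the conjugate as applying to channel j. The true range of the printed quantity is -1 to +1, with the sign set by channel order.

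The consequence for the graph measures is conditional. It arises only if the scripts follow the printed formula and apply a positive cut-off to signed values. Under the assumed example, about half of the edges in one triangle would be lost; the share in real data would depend on the lags, the noise and the cut-off.

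Severity is low. The outcomes affected are the secondary wPLI-based connectivity and graph measures. The δ-wave metrics, BIS, NOL and microstates do not use the index. The dPLI matter is a request for clarification and not an error.

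**What to change.** In section 3.4, print wPLI = |E{Im C}| / E{|Im C|}, with the matching outer bars on the second form. This yields the stated range and a symmetric matrix for section 3.5.

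Check the analysis scripts against this definition with one simulated pair: a constant non-zero lag must return 1 in both channel orders.

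Add one clause to the dPLI definition saying that the phase difference is taken into (-π, π] before the Heaviside step. Section 3.7.2 lists the direction of frontoparietal connectivity among the network measures, so the convention is worth stating.

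The cost is two lines of text and a short code check. No data collection, sample size or outcome changes.

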### Graph theoretical properties

3.5

For each frequency band, wPLI matrices will be thresholded into adjacency matrices, and graph-theoretical analyses will be performed. Core measures will include global efficiency (Latora and Marchiori, 2001), clustering coefficient (Watts and Strogatz, 1998), modularity (Newman, 2006), and small-worldness (Humphries and Gurney, 2008). Network hubs will be identified using node degree and betweenness centrality, reflecting the integration role of highly connected nodes (Van Den Heuvel and Sporns, 2013). Particular focus will be given to frontoparietal connectivity, which is strongly implicated in anesthetic-induced unconsciousness (Lee et al., 2013).

### Micro-state analysis

3.6

To examine the fast temporal dynamics of large-scale cortical activity, we will perform an EEG microstate analysis. Microstates represent brief, quasi-stable scalp potential topographies thought to reflect coordinated activity within distributed neural networks (Lehmann et al., 1987; Michel and Koenig, 2018). Global field power (GFP) peaks will be identified from bandpass-filtered data, and the corresponding maps will be clustered using k-means to extract four canonical microstate classes (A-D) (Koenig et al., 2002). The continuous EEG will then be back-fitted to these templates to derive standard temporal parameters: mean duration, occurrence rate, coverage, and transition probabilities.

Comparisons across depth of anesthesia and stimulation blocks will reveal whether CLAS alters the stability or sequencing of cortical microstates, providing a complementary perspective to the spectral and connectivity analyses.

### EEG and statistical analyses

3.7

#### Effect of CLAS on *δ*-waves morphology and topography

3.7.1

EEG data will be processed at the level of individual channels to characterize the impact of CLAS on δ-wave morphology and topography using custom Python scripts. Each detected δ-wave will be segmented as a single event (250–10,000 ms duration), and morphology will be quantified by amplitude, slope, transition frequency, density, and power spectral density (Bouchard et al., 2021). These metrics will be compared across conditions (*in-phase*, *anti-phase, sham*) and cortical regions of interest (frontal, central, midline, parietal, temporal, occipital). Descriptive statistics will be computed at both the subject and group level, with comparisons assessed using repeated-measures ANOVA and independent-samples *t*-tests, including age and sex as covariates.

Topographical EEG maps will be generated for canonical frequency bands (delta (0.1–4 Hz), theta (4–8 Hz), alpha (8–13 Hz), beta (13–30 Hz)), and phase-amplitude coupling measures will be calculated to further assess condition-dependent differences in oscillatory dynamics. Topographical mapping will allow testing for regional differences, as frontal predominance of *δ*-waves is a hallmark of both sleep and propofol anesthesia (Murphy et al., 2011; Purdon et al., 2015). To extend beyond scalp measures and as an exploratory aim, source estimation will be performed using standardized head models (Michel and He, 2019). Finally, propagation analyses will be conducted to quantify directionality of δ-wave travel across the cortex, as slow oscillations are known to spread as traveling waves and have been proposed as indices of large-scale cortical communication (Massimini et al., 2004; Tononi and Massimini, 2008).

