**Methods:**

We describe a prospective, within-subject protocol in 30 neurologically healthy adults undergoing elective surgery under propofol GA. Intraoperative high-density electroencephalography (hd-EEG; 128 channels) is recorded while a real-time CLAS algorithm detects *δ*-waves at the Fz electrode, and triggers pink-noise bursts in three conditions: *in-phase* (peak-locked), *anti-phase* (trough-locked), and *sham*. An extended *in-phase* block is then combined with a standardized tetanic nociceptive stimulus (100 Hz, 70 mA, 30 s) to test robustness under an arousal challenge. Depth of hypnosis is monitored with the Bispectral Index (BIS), and nociceptive/autonomic reactivity with the Nociception Level (NOL) index. Primary outcomes quantify *δ*-wave morphology and SWA (amplitude, slopes, duration/frequency, transition frequency, density, power spectral density), along with topography, source estimation, and propagation. Secondary outcomes include depth of anesthesia (BIS), nociceptive balance (NOL), functional connectivity (weighted and directed phase-lag indices), graph-theoretical organization (global efficiency, clustering, modularity, small-worldness), and EEG microstates (duration, coverage, transitions).

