### δ-waves metrics

3.3

Figure 4 illustrates some of the different metrics that are described in the following section. *Amplitude (μV):* The peak-to-peak amplitude was calculated as the absolute difference between the maximum and minimum values of the oscillation: 
$A_{e1-e2}=|V_{e1}-V_{e2}|$
, where *V_e1_* is the value of the first extremum in μV, and *V_e2_* is the value of the second extremum in μV. *Frequency (Hz)*: The mean frequency of the oscillation was defined as the inverse of its duration: 
$F=\frac{1}{d}$
. *Slopes (μV/s)*: We calculated three slope measures to quantify the rate of voltage change within each oscillation: (1) 1st zero-crossing to 1st extremum: 
$\text{slop}e_{\mathrm{zc}[i]\_e1}=\frac{|V_{e1}|}{t_{e1}}$
, (2) 1st extremum to 2nd extremum: 
$\text{slop}e_{e1\_e2}=\frac{A_{p-p}}{|t_{e1}-t_{e2}|}$
, (3) 2nd extremum to last zero-crossing: 
$\text{slop}e_{e2\_\mathrm{zc}[i+1]}=\frac{|V_{e2}|}{d-t_{e2}}$
, where *t_e1_* and *t_e2_* are the time (in seconds, relative to the initial zero-crossing) at which the first and second extremum occur, respectively. *Transition Frequency (Hz):* The transition frequency was defined as the inverse of twice the interval between the first extremum and the second extremum: 
$F_{\text{trans}}=\frac{1}{2|t_{e2}-t_{e1}|}$
. *Density (SOs/s)*: The density of delta waves (*δ*-waves) was defined as the number of δ-waves per second over the full duration of the recording: 
$\text{Density}=\frac{N_{\mathrm{\delta W}}}{T}$
, where *N_δW_* is the total amount of δ-waves detected in the recording, and *T* is the total duration of the recording in seconds.

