#### Association of CLAS with depth of anesthesia

3.7.2

Depth of anesthesia will be evaluated using the BIS index, an EEG-derived index validated for intraoperative monitoring (Connor, 2022; Rampil, 1998). BIS index values will be compared across *in-phase*, *anti-phase*, and *sham* blocks using repeated-measures ANOVA and pairwise paired *t*-tests with Holm–Bonferroni correction, to control for multiple comparisons. To probe the relationship between the BIS index and underlying cortical dynamics, correlation analyses will be run between BIS values and *δ*-wave features (amplitude, slope, spectral power), building on prior evidence that BIS partly reflects the presence and strength of slow oscillatory activity (Akeju and Brown, 2017; Bruhn et al., 2000). To further dissociate oscillatory modulation from global state-dependent spectral changes, the aperiodic (1/f) parametrization will also be extracted for each block and examined in relation to BIS values (Donoghue et al., 2020; Lendner et al., 2020).

The impact of CLAS large-scale neural dynamics during general anesthesia will also be quantified through EEG-derived network measures, including functional connectivity (wPLI, Vinck et al., 2011; dPLI, Stam and Van Straaten, 2012) and graph-theoretical properties (network motifs; degree and direction of frontoparietal connectivity; Lee and Mashour, 2018). We will also investigate the effect of CLAS on EEG microstates in order to characterize the temporal dynamics of whole-brain neuronal network.

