#### CLAS and nociceptive stimulation

3.7.3

Because nociceptive stimulation will be delivered only during *in-phase*, the primary analyses will assess within-subject changes across the *Pre-Pain*, *Pain*, and *Post-Pain* epochs. As a first step, *δ*-wave morphology will be quantified by comparing amplitude, slope, and power spectral density (PSD) across the three conditions, since these features provide sensitive markers of cortical arousal and nociceptive disruption under anesthesia (Bonhomme et al., 2016; Plourde et al., 2006). To dissociate band-limited power changes from broadband spectral shifts that can occur under propofol anesthesia, we will additionally parameterize the aperiodic (1/f-like) component of the EEG power spectrum for each stimulation block. Power spectral density will be estimated per block and channel, and the aperiodic exponent (slope) and offset will be extracted over a predefined frequency range using spectral parameterization methods. These aperiodic parameters will be compared across *in-phase, anti-phase*, and *sham* conditions and, where relevant, included as covariates when interpreting *δ*-band power changes.

The primary analysis of nociceptive reactivity will be changes in the NOL index and time-to-recovery. Secondary analysis will examine changes in mean arterial pressure (MAP), heart rate (HR), and BIS index values. Source localization and propagation analyses will further characterize the cortical generators and spatiotemporal spread of δ-waves during nociception (Massimini et al., 2004; Murphy et al., 2011).

Statistical models will include linear mixed-effects analyses with Condition (*Pre-Pain*, *Pain*, *Post-Pain*) as a fixed factor and age, and sex. *p*-values will be corrected for multiple comparisons using familywise error correction. This design enables testing whether *in-phase* CLAS can preserve *δ*-wave integrity and stabilize autonomic reactivity in the presence of nociceptive input, a key criterion for balanced anesthesia (Garcia-Larrea and Bastuji, 2018).

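### The primary aim (SA1) has several unranked primary outcomes and no multiplicity correction, although the BIS pairwise tests and the pain-epoch models have one

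*Protocol article*

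**What the plan says.** The Abstract (Methods) gives the primary outcomes as δ-wave morphology and slow-wave activity ("amplitude, slopes, duration/frequency, transition frequency, density, power spectral density), along with topography, source estimation, and propagation"). None is ranked. Section 1.8 (SA1) and section 4.1 (H1) predict changes in several of these metrics, again without a lead metric.

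Section 3.7.1, the SA1 analysis, says that "morphology will be quantified by amplitude, slope, transition frequency, density, and power spectral density". The metrics are compared across in-phase, anti-phase and sham and across "cortical regions of interest (frontal, central, midline, parietal, temporal, occipital"), using repeated-measures ANOVA and t-tests with age and sex as covariates. No correction is mentioned. Section 3.3 adds that slope is not one quantity: "We calculated three slope measures to quantify the rate of voltage change within each oscillation".

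Two other analyses do carry a correction. In 3.7.2 the pairwise BIS t-tests have a Holm–Bonferroni "correction, to control for multiple comparisons". In 3.7.3, directly after the Pre-Pain/Pain/Post-Pain mixed model, the p-"values will be corrected for multiple comparisons using familywise error correction".

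The status of source estimation differs between places. The Abstract lists it among the primary outcomes, while 3.7.1 says: "To extend beyond scalp measures and as an exploratory aim, source estimation will be performed using standardized head models".

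**The concern.** The article sets multiplicity control analysis by analysis. It does so for the BIS contrasts and for the pain epochs, and leaves it out for the primary aim. SA1 also has no single primary test that could make a correction unnecessary. The analysis as written therefore has no stated familywise error rate, and nothing says which result, or how many, would confirm H1.

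The stake is the study's main conclusion. The Discussion says that confirmation would position CLAS as the first neuromodulatory technique to amplify anesthetic δ-waves directly. That conclusion rests on SA1.

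Some metrics also share components, so one underlying change can appear in several of them. This should be borne in mind before agreement across metrics is read as repeated confirmation.

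**Working it through.** **Inputs from the document**
- Metrics in 3.7.1: amplitude, slope, transition frequency, density, PSD = 5. With the three slopes of 3.3 counted separately: 7.
- Regions in 3.7.1: 6.
- Conditions: 3, giving 2 contrasts against sham.
- Patients: 30, within-subject (section 2.1.2).

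**Assumptions, because the document gives no figure**
- Two-sided alpha of 0.05 per test, each test holding that size, as a repeated-measures ANOVA or paired t-test would.
- The correlation between tests, shown as a range.
- The number of tests, because 3.7.1 does not say whether region is an ANOVA factor or whether each region is tested separately.

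The plan states no error rate, so there is no figure of its own to reproduce. The sample size of 30 is justified by feasibility, literature and the within-subject design, with no alpha, power or effect size.

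**Formula.** For k independent tests, P(at least one false positive) = 1 − 0.95^k. Correlated cases come from simulation under the global null.

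**Narrow count: one test per metric**
- k = 5: 1 − 0.95^5 = 22.6%. At common correlation 0.5 about 18%, at 0.8 about 13%. A paired simulation with n = 30 and correlation 0.8 between metrics gives 12.3%.
- k = 7: 1 − 0.95^7 = 30.2%. At 0.5 about 23%, at 0.8 about 15%.

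Range: about 12–30%.

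**Wide count: every metric, region and sham contrast tested separately**
- 5 × 6 × 2 = 60 tests: 1 − 0.95^60 = 95.4%. The paired simulation, with metric/region correlations in that order, gives 87% at 0.3/0.5, 73% at 0.5/0.7, 57% at 0.7/0.8 and 44% at 0.8/0.9.
- 7 × 6 × 2 = 84 tests: 1 − 0.95^84 = 98.7%. With one common correlation for all tests: about 74% at 0.5, 47% at 0.7 and 35% at 0.8.

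Range: about 35–99%.

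**In-phase versus sham only, predicted direction only** (5 metrics × 6 regions, 2.5% in that direction): 1 − 0.975^30 = 53% if independent, and 37%, 25%, 18% and 13% at the four correlation settings above.

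**Shared components in the metrics (section 3.3).** The middle slope is A/|t_e1 − t_e2| and transition frequency is 1/(2|t_e2 − t_e1|). Hence slope = 2 × A × F_trans for each wave. The identity holds wave by wave, not for subject means, and it makes slope a product of two metrics, not a duplicate of either. It is a reason to give weight to the correlated figures.

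**Effect of control.** A single named primary test has error 5%. Bonferroni over the 60 tests (0.05/60 = 0.00083) gives a simulated familywise error of 2.0–4.5% across the same settings.

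**The case against.** The strongest reply is that the wide count is not the documented analysis. Region can naturally be read as an ANOVA factor, in which case the first look at each metric is one condition effect, and 5 to 7 tests is the fairer count. This stands, and is why the narrow range is given. It does not remove the problem. The narrow range still exceeds 5%, the t-tests are not made conditional on the ANOVA, and an omnibus test within a metric does not control error across metrics.

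A reader might infer that a false positive claim is likely, meaning more probable than not. The document does not support that. At high correlation even the wide count falls below one half, and the narrow count never reaches it.

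A reader might also infer that one significant metric in any region would be taken as confirming H1. No such rule is written. H1 is a directional pattern with frontal predominance, which an isolated occipital finding would not match. What can be said is that no decision rule is stated.

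Nor can it be said that both secondary aims are fully corrected, or that SA1 is the largest family. In SA2, Holm–Bonferroni attaches only to the BIS pairwise tests. The BIS correlations, connectivity, graph and microstate measures carry no stated correction, and they are numerous.

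The familywise sentence in 3.7.3 might be read more broadly, since that section also compares aperiodic parameters across in-phase, anti-phase and sham. But it directly follows the pain-epoch model, and nothing extends it to 3.7.1.

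Finally, this is a condensed article on a 30-patient, feasibility-sized study, and an unseen analysis plan may hold a hierarchy. That tempers the point. It does not answer it, because the article itself fixes corrections for other analyses, presents an unranked list as primary, and labels source estimation in two ways.

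**Conclusion.** The point holds in this form: SA1 has several unranked primary outcomes, no lead metric, region or contrast, no rule for confirming H1, and no multiplicity correction, whereas the BIS pairwise tests and the pain-epoch models have one. Source estimation is labelled inconsistently.

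The chance of at least one false positive is about 12–30% on the narrow count and about 35–99% on the wide one. Every figure calculated is above 5%, but no single figure should be quoted as the error rate of this plan.

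These figures rest on the assumed alpha, test count and correlations, and on each test holding its nominal size. The independent-samples t-tests that 3.7.1 names would not hold it on within-subject data. They run below nominal size when a patient's blocks are positively correlated, so rates for those tests would be lower. That is a separate matter.

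**What to change.** In 3.7.1, and fixed before analysis:

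- Name one primary metric, region and contrast. One example is peak-to-peak amplitude in the frontal region, in-phase versus sham, two-sided 5%. The choice belongs to the investigators; what matters is that it is made in advance.
- Test anti-phase versus sham on the same metric and region next, in fixed sequence.
- Put the remaining SA1 metrics and regions under Holm or a max-statistic permutation test, or label them exploratory.
- Label source estimation exploratory in the Abstract as well.

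This costs about a paragraph. A single primary test at 5% gives up no power: with 30 paired observations and 80% power, the detectable standardized difference is 0.53. The downside is a stricter threshold for the non-primary SA1 metrics. For example, the first Holm step over five metrics is 0.05/5 = 0.01, at which the detectable difference rises to 0.66.
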